**Satakunta Central Hospital**

Team leader [name], PhD, orthopaedics and traumatology

Participating researcher [name]

1. **BACKGROUND**

The impact of degenerative musculoskeletal diseases on individual people and on the society as a whole will increase dramatically in the future across the world due to the increasing age and more sedentary lifestyle of most western populations [1]. Most common osteoporotic fractures are distal radius fracture (DRF), proximal humerus and hip fractures. Although operative treatment of hip fractures is universally accepted, severe discrepancies exist on the treatment policies of the most common upper extremity fractures, distal radius, among the elderly people [2].

Distal radius fractures (DRF) can be categorized to stable or unstable fractures. A stable fracture maintains dorsal tilt, radial height, radial inclination, ulnar variance and carpal malaligment during conservative treatment whilst during cast treatment of an unstable fracture a displacement will eventually occur. In these cases, fracture reduction and anatomical restoration is often acceptable after manipulation and cast application but it will be lost during the treatment. This loss in fracture reduction can occur early (< 1-2 week) or late (at 6 weeks) [3]. Late instability presents a particularly complex problem to clinicians because early radiographs may show good reduction but later fracture might still collapse and lead to functionally disabling malunion. These unstable fractures account for about 30-60% of all DRFs [3-5]. However, since the reason for instability is multifactorial, there is no simple way to predict fracture healing [4-12].

The purpose of conservative treatment is to stabilize the fracture with cast, brace or other external supports where the bone is allowed to heal anatomically. Immobilization should also relieve pain. Several different methods of immobilization have been described [13-18]. Historically most often used method is closed reduction and immobilizing the wrist into slight flexion-ulnar deviation-pronation –position. The flexion -position was first described by Frederic J. Cotton in 1910 [19]. Although the method was commonly used in that era there was growing evidence that a strict wrist flexion could lead to median nerve compression. In 1933 Abbott and Saunders noticed that reduction in flexion increases resistance for dye flow in cadaver carpal tunnels [20]. Later the method was condemned as ‘Cotton-Loder’ position and since then the absolute flexion has been abandoned. Slight flexion-ulnar deviation position was, however, considered to be beneficial for maintaining the fracture reduction during immobilization. It was suggested that in this reduction position the soft tissue envelope around the fracture fragments and the distraction produced by radiocarpal ligaments (ie. ligamentotaxis) could resist the dislocating forces generated over the fracture line. In 1950 Sir John Charnley published his classic and highly influential guideline “The Closed Treatment of Common Fractures” [21]. In his book Charnley described the use of 3-point technique to immobilize the fracture in a slight flexion-ulnar deviation-pronation position. This technique has been widely adopted worldwide by several leading authors in important textbooks of orthopaedics and hand surgery until the recent years.

However, in clinical practice the flexion-ulnar deviation reduction position causes common extensor tendons to be tightened and thereby not allowing proper finger flexion during treatment. This is problematic especially among elderly people in whom degenerative joints are vulnerable to immobilization- induced stiffness. The median nerve compression, the most common complication in DRF, is also been seen n patients with increased carpal tunnel pressure. The pressure has been shown to increase three-fold when changing the neutral cast immobilization position to flexion [22-24].

Other methods of immobilization are functional bracing, immobilization wrist in neutral and slightly extended position as well as in pronation or in supination [13-16]. Cochrane database review regarding conservative treatment of DRF in adults concluded that there is insufficient evidence from randomised trials to determine which method of conservative treatment is the most appropriate when treating most common types of adult DRF [24].

It has been suggested that fracture stability during conservative treatment is not related to cast or immobilization position properties but merely ‘inherent’ characteristics of fracture as well as the patient [4,9-12,24]. Current evidence also indicates that the functional outcome of DRF in elderly people (>65) is not related to anatomic alignment of the fracture [25-30]. Weak evidence supports neutral (radius-metacarpal line 0°) or functional (radius-metacarpal line 20° of extension) reduction [17,18,24]. This practice has been adopted by several countries in their guidelines of DRF treatment. However, the evidence supporting this position is scarce and there are no high quality RCT studies in the English language literature comparing commonly used slight flexion-ulnar deviation -position and functional position.

Functional outome in DRF patients can be affected other than fracture alignment or other fracture spesific factors as well. Pain catastrophizing and fear to use injured limb are shown to increase disability, increased pain and muscle weakness in upper extremity and DRF patients [31-34]. The severity of acute pain, catastrophic thinking and trauma related anxiety has been shown to associate with finger stiffness after DRF [35]. Pain catastrophizing scale (PCS) is one of the most widely used measure of catastrophic thinking related to pain [36]. PCS has been translated into several languages and is widely incorporated in the assessment protocol of pain clinics and rehabilitation centres. However, pain catastophizing as a predictor of funtional outcome has not been previously studied with consevartively treated DRF in elderly people.

1. **OBJECTIVES**

The aims of the present pragmatic collaboration study on the conservative treatment of DRFs are:

1. to compare two cast position (volar flexion, ulnar deviation cast position and functional cast position) by means of functional outcome measured with patient rated wrist evaluation (PRWE) score in persons aged 65 or more.
2. to compare pain, disability, quality of life, grip strength, number of complications and cast changes after DRF treated with these two different cast positions
3. to assess the effect of PCS on the functional outcome of conservatively treated DRFs and the possible interaction between PCS and the functional outcome of DRF treatment with two different cast positions
4. **PRIMARY HYPOTHESES**

Our primary null hypotheses are as follows:

1. functional cast position gives similar functional outcome than currently used flexion-ulnar deviation cast position
2. functional cast position yields to similar results to currently used flexion-ulnar deviation cast position with regard to quality of life and grip strength and also with lower rates of complications and number of cast changes during immobilization when treating DRFs.
3. high PCS does not have an interaction with functional outcome on the patient rated wrist evaluation (PRWE) scale after adjusting for cast position used in the conservative treatment
4. **STUDY DESIGN**

The study is a pragmatic, prospective, randomized, controlled, multi-center trial. It is aimed to compare two different positions of a cast. The two cast positions compared are flexion-ulnar deviation position (widely used in Finland) and functional position used in other Nordic countries.

Primary outcome in this study is PRWE score measured after one and two years. Secondary outcomes measured are disability [Quick-DASH (disabilities of the arm, shoulder and arm)], pain in visual analogue scale (VAS), PCS, quality of life (15-D), complications and number of surgical interventions and cast changes. Subgroup analysis will be performed to find out patient specific features indicating good or worse outcome. PCS is used to assess the presence of possible mental susceptibility possibly influencing to the functional outcome.

1. **RESEARCH METHODS AND MATERIAL**
   1. **PATIENT SELECTION**

The eligible study population will consist of all consecutively (aged 65 or more) treated patients with a DRF identified in the public or referral emergency departments of participating hospitals.

**Following criteria is used in patient selection:**

Inclusion criteria:

- low energy intra- or extra-articular dorsally displaced DRF within 3cm of the radiocarpal joint, diagnosed with lateral and posterior-anterior radiographs in emergency room (ER)
- physician on call (general practician (GP), acute physician, orthopedic resident or orthopaedic consultant) thinks patient could be appropriate for conservative treatment

Exclusion criteria:

- Operative treatment
- Refuse to participate the study
- Open fracture more than Gustilo 1 gradus
- Age 64 or less
- Chauffeure’s or Barton´s fracture
- Smith´s fracture (volar angulation of the fracture)
- Does not understand written and spoken guidance in local languages
- Pathological fracture or (previous) fracture in the same wrist, antebrachium or elbow
  1. **RANDOMISATION**

All patients will be randomized before closed reduction of displaced fractures and immobilization without reduction of non-displaced fractures to either functional cast or flexion-ulnar deviation cast for 5 weeks. Patients will be randomized using a random number matrix in block allocation fashion. The blocks will be stratified by the known associations; age, centre and intra or extra-articular fracture line. The treatment allocations from the matrix will be sealed in envelopes, which are located in the ER. After the patient´s enrollment has been confirmed and informed consent is signed, a medical orderly specialized in casting will open the envelope and make the cast as allocated. The medical orderlies responsible for the casting will not participate in other ways in the study.

The research coordinator will monitor the study flow. An independent monitoring committee has been established.

- 1. **INTERVENTION**

DRFs are in everyday life treated by health care center physicians, experienced acute physicians, and trauma surgeons, thereby; we do not see any reason to limit the number of on call physicians or education or experience of on-call physician in this pragmatic trial.

Closed reduction is done under local anaesthesia by injecting Lidocaine 1% into fracture area. The technique of closed reduction is not limited to any specific technique. Fluoroscopy can be used when performing closed reduction if it is available in the participating center. Cast reduction position examples are delivered to participating centers to assure correct position of casting. After closed reduction, additional radiographs will be taken to confirm the reduction of the fracture. After physician on-call has accepted the fracture to be treated conservatively, a dorsal splint for 5 weeks is used. Non-displaced fractures are immobilized according to randomization without reduction.

After the allocation and preparing the cast, the patient is asked to fill the PCS questionnaire.

- 1. **FOLLOW-UP**

Follow-up visits are being conducted in primary health care centers as seen necessary by the physician on-call. They are arranged by the regional guidelines, at 1 and 2 weeks with radiographs. Due to the pragmatic nature of the trial we will not set any angulation degrees or shortening limits indicating operative treatment if reduction is lost during the follow-up. Whether the achieved angulation and/or possibly restored shortening is lost during the follow-up, the decision to consult local orthopedist or hand surgeon is left to the discretion of treating physician. Moreover, if patient has been referred for operative treatment from the primary care by the physician on-call but conservative treatment is chosen in the referral center ,the patient is still eligible for the study. Follow-up of these patients is conducted in the primary care or hospital based on local protocols. Since patients will be randomized in blocks by the hospital, we will assume that randomization will take care of the possible differences between centers.

**Figure**: Flow chart of the trial.

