**Enrollment**

**5 w follow-up**

**1+2 y Follow-Up**

Allocation to volar flexion & ulnar deviation cast and PCS

GP´s visit + x-ray if seen necessary by the physician on-call

Physician´s visit at study hospital, x-ray

 PRWE, QuickDash, VAS, PCS, 15-D ROM, grip

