**3 m Follow-Up**

GP´s visit and x-ray prior to cast removal

Mailed questionnaires, no physician´s visit

 PRWE, QuickDash, VAS, 15-D, PCS

Physician´s visit at study hospital, x-ray

 PRWE, QuickDash, VAS, PCS, 15-D ROM, grip

Excluded

Direct operative treatment

Refuse to participate the study

Open fracture more than Gustilo 1 gradus

Age 64 or less

Chauffeure’s or Barton´s fracture

Smith´s fracture (volar angulation of the fracture)

Does not understand written and spoken guidance in local languages

Pathological fracture or previous fracture in the same wrist, antebrachium or elbow

Pathological fracture or previous fracture in the same upper extremity

Allocation to functional cast and PCS

GP´s visit + x-ray if seen necessary by the physician on-call

Cast immobilization time will be 5 weeks according to current guidelines in Finland. The final physician’s visit will be at the time of the cast removal. All patients have an x-ray prior to cast removal. After cast removal, the decision to refer patient for physiotherapist will be left to discretion of the treating physician.

After three months the patient will visit orthopedic outpatient clinic in the hospital where the treatment was initially started (Table). This visit is part of the study protocol. During the visit a direct lateral and anteroposterior radiographs will be taken. PRWE, PCS, Quick-DASH, 15-D and pain in VAS will be assessed. The number of cast changes during treatment is queried from the patient and the number of changes is recorded.

The 1- and 2-year **follow-ups are executed with postal questionnaires in order to reduce patients’ discomfort and aiming to as easy-as possible handling of the follow-up data. Controls include** PRWE, VAS (for level of pain), PCS, Quick-DASH and 15-D.

At the 1 and 2 year follow-up complications will be recorded from patient records.

|  | **Medical history** | **Radiograph** | **PRWE** | **PCS** | **Pain** | **Grip** | **Quick-DASH** | **15-D** | **VAS** |
| --- | --- | --- | --- | --- | --- | --- | --- | --- | --- |
| **Baseline** | x | X |  | x |  |  |  |  |  |
| **1-2 weeks** | (x) | (x) |  |  |  |  |  |  |  |
| **5-6 weeks** | (x) | X |  |  |  |  |  |  |  |
| **3 months** | x | X | x | x | x | x | x | x | x |
| **1 year** |  |  | x | x | x |  | x | x | x |
| **2 years** |  |  | x | x | x |  | x | x | x |

(x) = taken if required by the treating GP

**Table**: Assessments and procedures of the trial.

- 1. **POWER ANALYSIS**

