In this trial, a validated wrist specific PRWE-score is used as the primary outcome measure. Just recently Wallenkamp and coworkers published a report, where minimal clinically important difference in PRWE was set at 11 points with SD of 14 [37]. Based on power calculations (Cl 95%, power 0.95, SD 14) required sample size per group is 40 patients. Assuming 30% of drop-out due to possible surgical interventions during cast treatment, group size would be 52 per group (total 104). In case of patient cross-over, patients will be analyzed according to the intention-to-treat principle.

- 1. **ANALYSIS OF THE MATERIAL**

Each patient will get an initial trial identification number (TIN) which is matched with actual patient identification (ID). **The matching key is stored in study nurse’s office in Tampere University Hospital. Patients are handled only with TIN during follow-up period and analyzing the of the material. Results are given only in general level with mean values thus individual patient’s information is not able to be extracted. The electronical registry contains x-rays and it is located in hospital’s secure server. The research data will be deleted 15 years after the end of the study.**

- 1. **STATISTICAL ANALYSIS**

Continuous skewed variables between the groups were compared by the Mann-Whitney *U* test and t-test is used when variables are unskewed. Results are presented with 95% confidence intervals. Two-way-tables with the chi-square test will be used for dichotomous variables. In subgroup analysis the effect of age, sex, fracture group, smoking, and other diseases will be evaluated against the scores and overall quality of life after fracture.

Analysis of covariance will be used to assess the effect of pain catastrophizing score on the outcome of cast treatment. PRWE will be used as a dependent variable, cast as independent and pain catastrophizing score as covariate.

The effect of cast position and PRWE is investigated also in the multivariate manner. Multivariable analysis is performed with linear regression analysis since the outcome variable PRWE is normally distributed. Main variable of interest included is the cast and age, sex, fracture group, smoking and other diseases are used as confounding variables.

- 1. **ETHICAL ISSUES**

The ethical approval of this study is applied with this research plan.

1. **IMPLEMENTATION**
   1. **CONTINGENCY PLAN**

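### The PCS scheduled as baseline is completed after allocation and casting, so the covariate for objective 3 can itself be affected by the cast

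*Protocol*

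**What the plan says.** The order of events is fixed in the protocol's Randomisation and Intervention sections.

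- Randomisation comes first: "All patients will be randomized before closed reduction of displaced fractures and immobilization without reduction of non-displaced fractures".
- Once consent is signed, "a medical orderly specialized in casting will open the envelope and make the cast as allocated".
- The first PCS follows: "After the allocation and preparing the cast, the patient is asked to fill the PCS questionnaire".

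The flow chart places PCS in the same position in both arms: "Allocation to volar flexion & ulnar deviation cast and PCS" and "Allocation to functional cast and PCS". The assessment table labels this PCS as baseline and repeats the scale at 3 months, 1 year and 2 years. The Study design section lists PCS among the secondary outcomes, and also says it is there to detect a mental susceptibility that may influence functional outcome.

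The third aim under Objectives is "to assess the effect of PCS on the functional outcome of conservatively treated DRFs and the possible interaction between PCS and the functional outcome" under the two cast positions. The Statistical analysis section serves that aim as follows: "Analysis of covariance will be used to assess the effect of pain catastrophizing score on the outcome of cast treatment". The model is then specified: "PRWE will be used as a dependent variable, cast as independent and pain catastrophizing score as covariate".

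**The concern.** A covariate or effect modifier in a randomised comparison should be fixed before treatment can act on it. Here the patient answers the PCS while wearing one of the two casts being compared. The protocol describes no blinding of patients, and a wearer can see and feel the wrist position.

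The Background section itself gives a reason why the arms might answer differently. It says that the flexed position tightens the extensor tendons, restricts finger flexion and raises carpal tunnel pressure. A scale about pain-related thinking, completed in that position, could pick some of this up.

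The score may then mix a patient trait with an early response to the cast. At stake is objective 3 and its null hypothesis: what the cast coefficient means once PCS is in the model, and whether a PCS-by-cast interaction can be read as effect modification by a pre-existing characteristic.

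**Working it through.** **Step 1: order of events.** The sections under *says* give: consent, envelope opened, cast made, PCS. Text and flow chart agree, and nothing in the protocol contradicts them. All four scheduled PCS values (baseline, 3 months, 1 year, 2 years) come after allocation and casting, so an analysis plan would have no pre-allocation value to choose.

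**Step 2: effect on the cast coefficient.** Let *s* be the shift in PCS caused by one cast relative to the other, and *b* the PRWE slope on PCS within arm. In a linear model with cast and PCS:

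adjusted cast effect = total cast effect − *b* × *s*

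This holds whether the shift is a real change that feeds through to PRWE or only a change in how the form is answered.

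**Step 3: size.** The protocol gives no figure for *s* or *b*, so both are assumptions. The size of the departure, *b* × *s*, in PRWE points is:

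| Assumed shift in PCS | Slope 4 points per SD | Slope 6 points per SD |
| --- | --- | --- |
| 0 SD | 0 | 0 |
| 0.2 SD | 0.2 × 4 = 0.8 | 0.2 × 6 = 1.2 |
| 0.5 SD | 0.5 × 4 = 2.0 | 0.5 × 6 = 3.0 |

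The Power analysis section uses a difference of 11 points, so the largest entry is 3.0 / 11 = 27% of the target and the smallest is zero.

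A second set of assumptions gives a similar picture. Take the protocol's PRWE SD of 14, an assumed PCS SD of 10, and an assumed correlation *r* between PCS and PRWE of 0.2 to 0.6. Then *b* = *r* × 14 / 10 = 0.28 to 0.84 PRWE points per PCS point. A shift of 0 gives no departure, a shift of 2 PCS points gives 0.56 to 1.68, and a shift of 4 gives 1.12 to 3.36. Simulated least squares with a total effect of 11, *r* = 0.6 and a shift of 4 returned an adjusted effect of 7.64, which is 11 − 3.36.

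**Step 4: effect on the PCS slope and the interaction.** Suppose observed PCS in one arm equals the undisturbed PCS plus a constant *s*, and that arm's PRWE is *a* + *b*₁ × (undisturbed PCS). Substituting gives (*a* − *b*₁ × *s*) + *b*₁ × (observed PCS). Only the intercept moves. The slope in each arm, and so the interaction, is unchanged.

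If the cast instead stretches the score by a factor (1 + *g*) in that arm, the slope becomes *b*₁ / (1 + *g*). A difference in slopes then appears even where none exists. Extra measurement noise in one arm would likewise flatten that arm's slope. Distortion of the interaction therefore needs an unequal effect across patients, or a change in what the score measures.

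**Step 5: which analyses use PCS.** The between-arm comparison of PRWE by t-test or Mann-Whitney test does not. The multivariable linear regression adjusts for demographic factors, fracture group, smoking and comorbidity, and PCS is not on that list. Only the ANCOVA and the interaction question are exposed.

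**The case against.** The strongest reply is that the ANCOVA is there to estimate the PCS effect, not the cast effect. A uniform shift is absorbed by the cast term and leaves the PCS slope and the interaction alone, as Step 4 shows. This stands, and it rules out the tempting reading that late collection by itself makes the interaction uninterpretable.

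A reader might also infer that the trial's main cast comparison is biased. The documents do not support that, because PCS enters neither the unadjusted comparison nor the listed regression.

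The size is open to challenge as well. A range that began at 0.2 SD would give 0.8 to 3.0 points, or 7% to 27% of 11, and would look like an expected bias. Nothing in the protocol excludes a shift of zero. The form is completed soon after casting, the stiffness described in the Background develops over the immobilisation period, and lidocaine given for reduction may blunt early discomfort. The figures are illustrations, not estimates.

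The ANCOVA does not name which PCS value it uses, but that alone can be left to a statistical analysis plan and is not the point here.

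Finally, a PCS taken before the envelope is opened precedes reduction and its local anaesthetic, so it may carry more acute pain. That is a genuine but small drawback. It applies equally to both arms and does not create a difference between them.

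What the reply does not remove is the timing. The only score labelled baseline is taken under treatment, and no analysis plan can supply a value that was never collected.

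**Conclusion.** The point holds with limited scope. The PCS intended as a measure of pre-existing susceptibility is a post-allocation measurement and can be affected by the cast. The PCS-adjusted cast coefficient should therefore not be read as the total cast effect. Under the stated assumptions (shift 0 to 0.5 SD, slope 4 to 6 PRWE points per SD) the two differ by 0 to 3 points, and by nothing if the cast does not move PCS.

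The PCS slope and the interaction are at risk only under the unequal or altered-measurement conditions in Step 4, which the documents neither establish nor exclude. The weakness is confined to objective 3 and is worth correcting because the correction is cheap.

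**What to change.** In the Intervention section, state that the patient completes the PCS after signing consent and before the allocation envelope is opened. Move PCS out of both allocation boxes of the flow chart to a point before randomisation. State that only this pre-allocation value serves as covariate in the ANCOVA and as modifier in the interaction analysis, and that later PCS values are treated as outcomes only.

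The cost is the same questionnaire given a little earlier in the emergency room, with no added form or visit.

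For patients already enrolled, report the first PCS by arm and show the unadjusted cast effect beside the PCS-adjusted one.
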